## Abstract

**Background:**

The promotion of well-being is an important goal of recovery oriented mental health services. No structured, evidence-based intervention exists that aims to increase the well-being in people with severe mental illness such as psychosis. Positive psychotherapy (PPT) is a promising intervention for this goal. Standard PPT was adapted for use with people with psychosis in the UK following the Medical Research Council framework for developing and testing complex interventions, resulting in the WELLFOCUS Model describing the intended impact of WELLFOCUS PPT. This study aims to test the WELLFOCUS Model, by piloting the intervention, trial processes, and evaluation strategy.

**Methods/Design:**

This study is a non-blinded pragmatic pilot RCT comparing WELLFOCUS PPT provided as an 11-session group therapy in addition to treatment as usual to treatment as usual alone. Inclusion criteria are adults (aged 18–65 years) with a main diagnosis of psychosis who use mental health services. A target sample of 80 service users with psychosis are recruited from mental health services across the South London and Maudsley NHS Foundation Trust. Participants are randomised in blocks to the intervention and control group. WELLFOCUS PPT is provided to groups by specifically trained and supervised local therapists and members of the research team. Assessments are conducted before randomisation and after the group intervention. The primary outcome measure is well-being assessed by the Warwick-Edinburgh Mental Well-being Scale. Secondary outcomes include good feelings, symptom relief, connectedness, hope, self-worth, empowerment, and meaning. Process evaluation using data collected during the group intervention, post-intervention individual interviews and focus groups with participants, and interviews with trial therapists will complement quantitative outcome data.

**Discussion:**

This study will provide data on the feasibility of the intervention and identify necessary adaptations. It will allow optimisation of trial processes and inform the evaluation strategy, including sample size calculation, for a future definitive RCT.

**Trial registration:**

Current Controlled Trials ISRCTN04199273 – WELLFOCUS study: an intervention to improve well-being in people with psychosis, Date registered: 27 March 2013, first participant randomised on 26 April 2013.

## Background

Developing a recovery orientation in mental health services is a policy goal in the UK and internationally [1]. Recovery is an individual process of gradual restoration from the illness, focusing on the resources and abilities of the individual instead of exclusively treating symptoms. Hence, supporting recovery from severe mental illness involves, in addition to treating symptoms, an increased emphasis on personal strengths [2], positive identity development [3], and the promotion of well-being [4].

Well-being is not only a central component of recovery from mental illness [5], its importance is further supported by research showing an association between well-being and improved functioning [6,7], increased resilience and life satisfaction [6], and suggesting its protective value against the onset or re-occurrence of mental illness [8,9]. There is strong evidence that well-being is not only a desirable outcome in its own right, but also a statistically significant predictor of symptomatic response in the treatment of people with psychosis [10,11] and strongly associated with medication compliance in this group [12]. Despite the relevance of well-being research to recovery [13], no structured intervention based on an empirically-defensible theory exists which targets well-being in people with severe mental illnesses such as psychosis [14].

The promotion of well-being is a focus of the academic discipline of positive psychology; one intervention based on this body of knowledge is positive psychotherapy (PPT). PPT was originally developed for depression as the target condition, following the hypothesis that depression can not only be treated effectively by reducing its negative symptoms but also by directly and primarily building positive emotions, character strengths, engagement, and meaning [15].

Evidence from intervention studies suggests that standard PPT is beneficial for people suffering distress or common mental disorders. Randomised controlled trials (RCTs) comparing PPT with no treatment show increased positive affect and life satisfaction and decreased depressive symptoms in undiagnosed students [16], in a self-referred online sample [8], in undiagnosed middle school students [17], and in students with a diagnosis of mild to moderate or severe depression [15,18]. PPT also showed statistically significant well-being gains and depressive symptom relief as compared to placebo therapy (e.g., recording early memories) in RCTs involving students with mild to moderate depression and in an undiagnosed community sample [15,19]. Further small studies from Iran (RCT) and Chile (quasi-experimental control group design) comparing PPT to behavioural therapy in patients with diagnosed depression showed PPT to be more effective in increasing happiness and decreasing depression [20,21]. Moreover, a meta-analysis of RCT evidence demonstrated that positive psychology interventions in general, including mindfulness, positive writing, hope, gratitude, forgiveness, kindness therapies, Fordyce’s Happiness Program, and PPT, statistically significantly improve well-being and decrease depressive symptoms for people with depression [22]. A dose–response effect was also present, with positive effect increasing with the number of different positive exercises in a therapy programme. Recently, a small uncontrolled feasibility study of PPT yielded promising results for people with psychosis in the US, statistically significantly increasing participants well-being, savouring beliefs, hope, self-esteem, and personal recovery scores [9].

Based on the above preliminary evidence, we adapted standard PPT [23] for use with people with psychosis in a UK context. The scientific framework for the study is the Medical Research Council (MRC) Framework for Evaluating Complex Health Interventions [24]. This involved a systematic review [14], a qualitative study [25], and an expert consultation to adapt the intervention and develop an intervention model to be tested in the present pilot RCT.The new intervention, i.e., WELLFOCUS PPT, has four target areas: increasing positive experiences, amplifying strengths, fostering positive relationships, and creating a more meaningful self-narrative. The WELLFOCUS model describes the intended impact of WELLFOCUS PPT, and is shown in Figure 1.

**Figure 1 F1:**
[figure not shown]
The WELLFOCUS model.

### Aims

The aim of this pilot RCT is to test the WELLFOCUS model. The three objectives are:

#### Objective 1: Piloting the intervention

To identify whether WELLFOCUS PPT is feasible and acceptable and determine any necessary modifications.

#### Objective 2: Piloting the trial processes

To test procedures for a future definitive RCT, especially in relation to eligibility criteria, randomisation procedures, allocation processes, and recruitment and retention rates.

#### Objective 3: Piloting the evaluation strategy

To test approaches to assessing fidelity, process evaluation, and outcome evaluation, to inform the design of a future definitive RCT including choice of primary and secondary outcome measures, and sample size calculation.

## Methods

### Hypotheses

While we shall conduct hypothesis testing, this is not the main objective of the study, as this is the purpose of the future definitive RCT. The reporting of the study will not therefore emphasise the results of hypothesis testing over the reporting of whether the objectives were met [26].Our hypotheses are derived from the WELLFOCUS Model shown in Figure 1. Regarding the effect of the intervention, we hypothesise that participants receiving the intervention will experience, compared to the control group, an improvement in well-being (primary outcome) and good feelings, symptoms, connectedness, hope, self-worth, empowerment, and meaning in life (secondary outcomes).

### Design

This is a single centre pilot RCT to test WELLFOCUS PPT in a group format in a convenience sample of people with psychosis. Patients are block-randomised to receive either WELLFOCUS PPT in addition to treatment as usual, or to continue to receive treatment as usual only. The design of this pilot RCT has been informed by recommendations for the conduct of pilot trials by Tabane et al. [27] and Lancaster et al. [28]. The Consort flow diagram [29] is shown in Figure 2.

**Figure 2 F2:**
[figure not shown]
Consort flow chart of WELLFOCUS RCT.

### Ethical approval

Ethical approval for the WELLFOCUS trial was obtained from the Camberwell St Giles Research Ethics Committee (reference 12/LO/1960). R&D approval was obtained from South London and Maudsley NHS Foundation Trust. Participants receive verbal and written information, and written informed consent is obtained from participants before they enter the study. The research is conducted in compliance with the Declaration of Helsinki [30].

### Study setting

Patients are recruited from seven teams and two research registers across the South London and Maudsley NHS Foundation Trust (SLaM). SLaM employs 4,500 staff in 296 teams, works with 34,128 service users, and provides adult mental health services across four Boroughs (Croydon, Lambeth, Lewisham, and Southwark). These services are provided through Clinical Academic Groups organised according to diagnoses; these groups bring together clinical services, research, education, and training for the benefit of patient care. This study takes place in the SLaM Psychosis Clinical Academic Group.

### Sample

#### Inclusion criteria

Patients are eligible to participate if they are aged 18–65 years, have a primary clinical diagnosis of psychosis, are using specialist mental health services, are not currently in prison, speak and understand English, and, in the opinion of their key clinician, are sufficiently well to participate in a group therapy.

#### Exclusion criteria

Patients with serious cognitive impairment preventing meaningful participation in a group intervention, and those who in the opinion of their key clinician are unable to give consent or are too unwell to be interviewed.

### Sample size

A sample size of n = 30 per arm has been recommended for pilot studies to estimate location (mean) and variability (standard deviation) of candidate outcome measures to inform later sample size calculation [28]. WELLFOCUS PPT is conducted as a group intervention with about 8 participants in each group. We aim to conduct five waves of PPT groups versus control, each starting with 16 participants (n = 8 in the intervention and n = 8 in the control arm), giving a total sample of 80. Allowing for a drop-out rate of 20%, consistent with attrition in a feasibility study of a similar intervention with service users with psychosis [9], this gives an analysable sample of n = 32 per arm to generate estimates for well-being as our primary outcome. However, we will try to minimize dropouts in our study as suggested by Little et al. [31].

The Warwick-Edinburgh Mental Well-being Scale (WEMWBS) was shown to have a one-week re-test reliability of 0.83 [32]. The correlation between baseline and 3-months follow-up can be assumed to be below that. Assuming a correlation of 0.7 the power to detect an effect size of 0.5 on the WEMWBS at follow-up, adjusted for baseline, would be at 0.80. A more conservative estimate of a correlation between baseline and follow-up of 0.6 would allow us to detect the same effect size with a power of 0.71. Higher effect sizes would provide higher power. For example, an effect size of 0.6 could be detected with a power of 0.85 assuming a correlation between baseline and follow-up of 0.6. All power calculations are based on a significance level of 0.05 and were calculated using the STATA 12.

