### Recruitment and randomisation

The study is introduced to all staff members in the participating teams. Care coordinators, key nurses or other appropriate staff members are asked to identify potentially eligible service users from their case load. Potentially eligible participants receive information about the study from the clinician. In addition, information about the study is sent to eligible service users on two research registers (which involves consent to be contacted by researchers). These are followed-up for recruitment via telephone by the research team. An appointment is scheduled for assenting participants from all sources with a member of the research team to provide further information on the study. In this meeting, the study is explained, written information is provided, and an opportunity is given to ask any questions. If the participant wishes to have time to consider participation, a second meeting is scheduled. Once the participant has given informed consent, baseline assessments are completed. Participants receive an ID number which is entered in the web-based randomisation system together with age (for validation). Some teams may have fewer than 16 eligible participants, and the minimum number of participants will be 8 (i.e., 4 per arm), with block for randomisation. Where possible we will over-recruit to a maximum of 20 participants in other teams. When participants from a participating clinical team have all been entered into the database, randomisation is conducted. Randomisation involves independent allocation to one of the two trial arms on a 1:1 basis. The use of stratification was considered disproportionate for a pilot RCT. The generation and implementation of the randomisation sequence is conducted independently by the King’s Clinical Trials Unit (registration number 053).

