#### Objective 3: Piloting the evaluation strategy

The usefulness of fidelity and process evaluation approaches will be determined by exploring whether researcher ratings of fidelity to the manual and process factors, such as engagement and beneficial effect of exercises, helps to improve prediction of outcome and future attendance as compared to recording group attendance only. The confidence interval approach will be used to help determine the suitability of the outcome measures and to inform the sample size calculation for a definitive RCT. This approach involves estimating the confidence interval of the difference between intervention and control group at follow-up, adjusted for baseline. The inclusion of zero (i.e., point of no effect) and the inclusion of a clinically relevant effect into the confidence interval will help to estimate the suitability of measures for a definitive RCT [28]. Further considerations to be taken into account for the choice of outcome measure for the definitive RCT will include the acceptability of the scale (as measured by the number of missing responses), the magnitude of correlation between baseline and follow-up on this scale, and the overall variance of the scale. The group means, standard deviations, and correlations between baseline and follow-up will be used to inform the sample size calculation for the definitive RCT.

In addition, outcomes will be analysed to estimate effectiveness of the intervention. This analysis will be done on an intention-to-treat basis, with participants analysed in the group to which they were randomised irrespective of their compliance with the assigned trial arm. To estimate effectiveness of the intervention, WEMWBS (primary outcome) at pre-treatment (baseline) and 3-month follow-up will be analysed using a random effects regression of outcome on trial arm adjusted for baseline score including a random effect to allow for between group variations in the intervention arm. Where relevant, we will also consider using other approaches to address missing data such as complier-average causal effect approaches [63].

Divergence of normality will be assessed for the distribution of all variables as will linearity of correlations and equality of variance. The choice of statistical methods will be adapted accordingly. *P* values of 0.05 will be considered significant in all cases. All analyses will be carried out in SPSS Version 20 and Stata Version 12.

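### The stated power (0.80, 0.71, 0.85) ignores therapy-group clustering that the primary analysis models, so the figures are upper limits

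*Protocol article*

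**What the plan says.** The Sample size section first sets the sample by a recommended 30 per arm for estimating means and standard deviations. It plans five waves of 16 participants (80 in total) and, after 20% drop-out, states that "this gives an analysable sample of n = 32 per arm".

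It then gives power for three scenarios. For the first, "the power to detect an effect size of 0.5 on the WEMWBS at follow-up, adjusted for baseline, would be at 0.80", at a correlation of 0.7. At a correlation of 0.6, power is put at 0.71 for an effect size of 0.5 and 0.85 for an effect size of 0.6. On method it adds only this: "All power calculations are based on a significance level of 0.05 and were calculated using the STATA 12". No ICC or design effect is mentioned.

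The same section states that "WELLFOCUS PPT is conducted as a group intervention with about 8 participants in each group". The analysis plan, under Objective 3, fixes the primary analysis as a regression of WEMWBS on trial arm, adjusted for baseline, "including a random effect to allow for between group variations in the intervention arm".

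**The concern.** Participants treated in the same therapy group share facilitators, sessions and each other, so their outcomes may be correlated. Controls have no such grouping. This is a partially nested design, and the analysis plan treats it as one. The variance of the treatment effect then contains a between-group component that is averaged over only about five groups. A power calculation for independent participants leaves that component out.

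What is at stake is whether the published power belongs to the analysis that will be run. With any positive ICC, the planned model is less sensitive than the Sample size section says.

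**Working it through.** **Inputs from the article.** 32 analysable per arm; 1:1 allocation; significance level 0.05; scenarios (d, r) = (0.5, 0.7), (0.5, 0.6) and (0.6, 0.6); five waves with about 8 intervention participants each. After 20% drop-out the analysed group size is 32/5 = 6.4.

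**Input assumed.** The therapy-group ICC, on the baseline-adjusted residual scale, in the intervention arm only. The article gives none; I show 0.01, 0.05 and 0.10.

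**Step 1: reproduce the stated figures.** For independent participants, in units of the outcome SD,

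Var = 2(1 − r²)/32, and power = Φ(d/√Var − 1.96).

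- d = 0.5, r = 0.7: Var = 2 × 0.51/32 = 0.0319, SE = 0.1785, d/SE = 2.80, power 0.800 (stated 0.80).
- d = 0.5, r = 0.6: Var = 2 × 0.64/32 = 0.0400, SE = 0.2000, d/SE = 2.50, power 0.705 (stated 0.71).
- d = 0.6, r = 0.6: SE = 0.2000, d/SE = 3.00, power 0.851 (stated 0.85).

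All three match. The alternatives tried do not: one-sided gives 0.88/0.80/0.91, change score 0.73/0.61/0.77, follow-up score only 0.52/0.52/0.67, and 40 per arm 0.88/0.80/0.92. So the stated figures use 32 per arm, a two-sided test, baseline adjustment and no clustering term.

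**Step 2: add clustering in the intervention arm only.**

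Var = (1 − r²)/32 × [1 + (6.4 − 1) × ICC] + (1 − r²)/32.

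The design effect in the intervention arm is 1.054 at an ICC of 0.01, 1.27 at 0.05 and 1.54 at 0.10. Worked example for d = 0.5, r = 0.7, ICC 0.05: Var = (0.51/32) × (1.27 + 1) = 0.0362, SE = 0.190, d/SE = 2.63, power Φ(0.67) = 0.75.

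| ICC | d 0.5, r 0.7 | d 0.5, r 0.6 | d 0.6, r 0.6 |
|---|---|---|---|
| 0 (as stated) | 0.80 | 0.71 | 0.85 |
| 0.01 | 0.79 | 0.69 | 0.84 |
| 0.05 | 0.75 | 0.65 | 0.80 |
| 0.10 | 0.70 | 0.60 | 0.76 |

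**Step 3: sensitivity to the reference distribution.** With five groups, a z test is optimistic. Satterthwaite degrees of freedom (4 for groups, 31 for controls) come to about 14 at an ICC of 0 and 12 at 0.05. Noncentral-t power is then 0.74/0.64/0.80 at an ICC of 0 and 0.67/0.58/0.73 at 0.05. The fall at an ICC of 0 comes only from the choice of degrees of freedom, so these rows should not be read as the effect of clustering alone.

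**The case against.** The strongest reply is that the sample size does not depend on the power figures. It is set by the 30-per-arm estimation recommendation and the five-wave structure, and power comes afterwards as illustration. The Hypotheses section says that testing is not the main objective and will not dominate reporting. The analysis plan judges outcome measures by confidence intervals. All of this stands, and it limits the severity.

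It is also fair that the size of the shortfall is not known. At an ICC of 0.01 the loss is about one point, and five equal groups is an idealisation, since Recruitment and randomisation allows 8 to 20 participants per team. Nor is there any arithmetic slip: the figures are correct for the model they assume.

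Three stronger readings are tempting, and the article does not support them.

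- **That the design certainly falls short by a known amount.** With no ICC given, only the direction is certain.
- **That a null WEMWBS result would be over-interpreted.** Interpretation is tied to the confidence interval from a model that does include the group effect.
- **That the definitive trial will inherit the omission.** The inputs listed for its sample size are means, standard deviations and correlations, but the planned model itself yields a between-group variance estimate, and nothing rules out its use.

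A degrees-of-freedom method is also commonly left to the statistical analysis plan, which is not shown, so its absence here is no fault.

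None of this removes the mismatch. The article chose to state three power figures, and they belong to a model other than the one it specifies.

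**Conclusion.** Wrong as written, of moderate severity. The figures 0.80, 0.71 and 0.85 treat 64 participants as independent, while the article delivers treatment in groups and models group variation. They are upper limits, reached only with an ICC of zero and a large-sample z test.

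On the normal approximation, the loss against the stated figures is about 1 to 2 points at an ICC of 0.01, 5 to 6 at 0.05 and 9 to 11 at 0.10. This assumes five equal groups of 6.4 analysed, 32 independent controls and an ICC on the baseline-adjusted scale. A small-sample correction would lower power further. The target of 80 is not called into question.

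**What to change.** In the Sample size section, do one of two things:

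- restate power for the partially nested design (about five groups of 6.4 analysed against 32 independent controls) over a declared ICC range, for example 0 to 0.10; or
- keep the present figures and label them as ignoring therapy-group clustering, hence as upper limits.

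Keep n = 80 and say that it rests on the estimation rationale. If the restated power uses a small-sample degrees-of-freedom method, name it; otherwise that choice can stay with the statistical analysis plan.

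The cost is a few sentences and a less favourable stated power. Recruitment, randomisation and trial conduct do not change, and no extra patients are needed.

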### Control group

Control group participants receive treatment as usual, consistent with the Care Programme Approach [33]. This includes systematic arrangements for assessing the health and social needs of people accepted into specialist mental health services, the formation of a care plan which identifies the health and social care required from a variety of providers, the appointment of a key worker to keep in close touch with the service user and to monitor and co-ordinate care, and regular review of and, where necessary, agreed changes to the care plan. Control group participants receive care from a multidisciplinary mental health team, and treatments may include medication, social or other individual or group-based psychological interventions. No psychological intervention based on positive psychology principles is currently provided.

